### **11.3 Data Management**

Independent, double-data entry will be performed into an electronic database by two different data capturers. Verification of the data will be performed after a comparison of the two entries. Data validation will include checks of limits, codes, missing data and logical inter- and intra-table consistency. Irresolvable inconsistencies will be referred to the investigational team for clarification. Upon completion of all validation processes, and after a blind review of the data, the database will be "locked". Data will be extracted from the database directly into data files for statistical analyses.

Modifications and updates to the database will be documented in an audit trail. All data management activities will be performed in a clinical data management system that is fully compliant with international and local guidelines and regulations pertaining to data management.

Medical and surgical history, concomitant illnesses and adverse events will be coded using the Medical Dictionary for Regulatory Activities (MedDRA) Version 12 or higher. Previous and concomitant medication taken at any stage during the study will be coded using the WHO Drug Dictionary (WHO-DD version 2011, quarter 1 or higher).

## **12 STATISTICAL ANALYSIS**

### **12.1 Statistical Program**

Statistical analyses will be performed using SAS® (Version 9.2 or higher, SAS Institute, Cary, NC, USA).

### **12.2 Endpoints**

#### **Primary Endpoint Variable**

- Induction of anti-Tat antibodies (IgM, IgG or IgA)

#### **Secondary Endpoint Variables**

- Physical examination data
- Vital signs data
- Adverse events

- Laboratory safety parameters
- Virology

### 12.3 Sample Size Determination

To evaluate the humoral immune response to vaccination, “responders” will be defined as those vaccinated subjects that develop an immune response above a specific cut-off level.

If positive response rates are 80% for the Tat vaccine group and 60% for the placebo group, with alpha set at 0.05 (2-tailed), a sample size of 91 per group will have 80% power of showing statistical significance ( $p < 0.05$ ). The assumed response rate for the Tat vaccine group is based on the results of phase I and ongoing phase II studies (Fleiss J.L. Tytun A., Ury S.H.K., A simple approximation for calculating sample sizes for comparing independent proportions, Biometrics, 1980).

Sample size was calculated using nQuery Advisor® software, version 6.01.

It is anticipated that approximately 10% of subjects will not complete the study. Therefore, a total of 200 subjects will be enrolled to ensure that 91 subjects per arm complete the study.

### 12.4 Population for Statistical Evaluation

Two groups of subject populations will be considered for statistical analysis:

- The **immunogenicity population**, representing all randomized subjects who received at least 2 vaccinations.
- The **safety population**, representing all randomized subjects who received at least one administration of Tat.

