| Study Objectives:    | Primary: To demonstrate that three 30µg doses of the Tat vaccine administered intradermally at 4 week intervals is immunogenic as compared to placebo in HIV-1 infected, anti-Tat antibody negative individuals on antiretroviral therapy.
Secondary: To monitor the safety of the Tat vaccine versus placebo in vaccinated volunteers.                                                                                                                                                                                                                                                                                                                                                                                                                                                                                                                                                                                                                                                                                                                                                                                                                          |
| Study Design:        | A Phase II, randomized, double-blind, placebo-controlled clinical trial.                                                                                                                                                                                                                                                                                                                                                                                                                                                                                                                                                                                                                                                                                                                                                                                                                                                                                                                                                                                                                                                                                            |

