| 
Interim Analyses
At least 50% of the original planned population (at least 100 subjects) will be included in an interim analysis. Data derived from the interim analysis will be used to re-calculate the sample size.
 
Statistical Analyses:
All statistical analyses will be performed using SAS® version 9.2 or higher. Two subject populations will be considered for statistical analysis:
 
 
1. The immunogenicity population, representing all randomized subjects who received at least 2 vaccinations.
 
2. The safety population, representing all randomized subjects who received at least one administration of Tat.
 
 
Primary Immunogenicity Variable
Induction of anti-Tat antibodies (IgM, IgG or IgA) as specific anti-Tat humoral immune response.
 
Secondary Variables
Adverse events, including any significant changes in hematological/biochemical/coagulation and urinalysis laboratory parameters.
Final analysis will be performed after all subjects have completed the study, the database has been locked, and the study has been unblinded.
                                                                                                                                                                                                                                                                                                                                                                                                                                                                                                                                                                                                                                                                                                                                                                                                                                                                                                                                                                                                                                                                                                                                                                                                                                                                                                                                                                                                                                                                              |

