#### **Secondary Objective**

To investigate the safety of three 30 µg doses of a therapeutic recombinant, biologically active, HIV-1 Tat protein vaccine administered intradermally at 4 week intervals, as compared to placebo.

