### 8.2 Secondary Endpoint Variables and Measurements

In order to evaluate the safety of the Tat protein vaccination schedule in the study population, the following secondary endpoints will be considered and compared between active and placebo groups:

- Changes in physical examination findings from baseline;
- Changes in vital signs from baseline;
- Adverse events (including local and systemic reactions to the vaccination schedule occurring during the course of the study);
- Changes in standard laboratory safety parameters from baseline

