### 12.7 Secondary Endpoint Analysis

Changes from baseline in physical examination results, vital signs data and laboratory parameters will be summarized for both treatment groups.

MedDRA dictionary will be used for coding adverse events. Adverse events will be summarized by system organ class, preferred term, severity and relationship with the

vaccination; the incidence of adverse events “possibly”, “probably” or “certainly” related to vaccination will be computed. All serious adverse events (SAEs) will be summarized by treatment group, subject, gender, age, duration of the event, action taken, investigator’s assessment of causality and outcome.

Change from baseline will be summarized for CD4+ T cells and HIV viral load. Haematology, clinical chemistry and urinalysis results will be graded according to Appendix I and will be presented for both treatment groups.

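### The safety population is defined by receipt of Tat, which leaves out every placebo recipient and removes the comparator from the safety analysis

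*Protocol*

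**What the plan says.** Section 12.4 names two analysis populations. The immunogenicity population is defined in arm-neutral terms, as "representing all randomized subjects who received at least 2 vaccinations". The safety population, in the next bullet, is defined by the active product: "representing all randomized subjects who received at least one administration of Tat". The synopsis repeats this: "The safety population, representing all randomized subjects who received at least one administration of Tat".

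Elsewhere the protocol describes safety as a comparison of the two arms:

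- **Section 3, secondary objective:** the safety of the three-dose regimen is to be investigated "administered intradermally at 4 week intervals, as compared to placebo". The synopsis words the same objective as "To monitor the safety of the Tat vaccine versus placebo in vaccinated volunteers".
- **Section 8.2:** for safety, "the following secondary endpoints will be considered and compared between active and placebo groups".
- **Section 12.7:** changes from baseline in "vital signs data and laboratory parameters will be summarized for both treatment groups". Serious adverse events are also summarized by treatment group, and graded laboratory results are presented for both groups.

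Section 5.1.2 assigns Group B three administrations of placebo and nothing else. Section 5.1 lists the placebo as the same buffer, sucrose and albumin as the vaccine, with no Tat protein.

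**The concern.** A subject in Group B never receives Tat, so the membership rule in section 12.4 cannot be met by anyone dosed correctly in that arm. The set that should carry the safety analysis then holds one arm only, while the objective, the endpoint section and the analysis section all require two.

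Safety is the only secondary objective. Participants are HIV-infected and on antiretroviral therapy, and sections 9.1.1 and 9.1.2.1 themselves warn that known adverse reactions to those drugs must be taken into account. The placebo arm is what allows such background events to be separated from effects of the vaccine. A safety table built on Tat recipients alone cannot do that.

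**Working it through.** The question is mainly one of applying the stated rule to each arm.

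**Inputs**

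- Planned enrolment and allocation: 200 subjects, 1:1, hence 100 per arm (synopsis; section 5.1.2).
- Group A: Tat 30 µg at weeks 0, 4 and 8. Group B: placebo at the same weeks (section 5.1.2).
- Placebo contains no Tat (section 5.1).
- Membership rule: randomized, and given Tat at least once (section 12.4; synopsis).

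**Applying the rule, everyone dosed as randomized**

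| Rule | Group A | Group B | Total |
|---|---|---|---|
| As written (at least one dose of Tat) | 100 | 0 | 100 of 200 (50%) |
| Arm-neutral (at least one dose of Tat or placebo) | 100 | 100 | 200 of 200 |

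Under the rule as written, the only Group B subjects who could enter are those given Tat by mistake. The between-arm difference in an adverse event rate is p_Tat − p_placebo. With 0 subjects in the placebo denominator, p_placebo is undefined and so is the difference.

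**Can Tat be read as either product?** The protocol uses the words vaccine and vaccination loosely for both arms, but it keeps Tat and placebo apart: in describing the doses (section 5.1), in storage (section 5.5) and in the blinded causality assessment (section 9.3.2). Within section 12.4 itself, one bullet uses the neutral word and the next uses Tat. A programmer would have textual grounds to treat that difference as deliberate.

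**Is there another set to fall back on?** Section 12.4 defines only the two populations. The immunogenicity set requires at least 2 vaccinations, and section 7.2 also removes the data of subjects who took prohibited medication during the 8-week treatment period. Used for safety, it would lose anyone who stopped after one dose, including anyone who stopped because of an adverse event.

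**Does any stated figure move?** The computed figure in section 12.3 is 91 per group for the primary endpoint, at 80% versus 60%, two-sided alpha 0.05 and 80% power.

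- Without continuity correction: n = [1.960 × √(2 × 0.7 × 0.3) + 0.842 × √(0.8 × 0.2 + 0.6 × 0.4)]² / 0.2² = 81.2, rounded up to 82.
- With the Fleiss correction: (81.2 / 4) × [1 + √(1 + 4 / (81.2 × 0.2))]² = 90.9, rounded up to 91.

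The stated 91 is reproduced and does not depend on the safety set.

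**The case against.** The strongest reply is that the intent is plain. Sections 8.2 and 12.7 specify a two-arm safety analysis, and no sentence in section 12.7 ties that analysis to the set in section 12.4 or says placebo subjects are left out. A statistician who followed section 12.7 alone would produce both arms. The protocol often uses active-product words for the blinded product in either arm, as in the preparation and administration steps, so Tat in section 12.4 reads like a slip for study product. Placebo subjects have the same safety assessments on the same schedule (Appendix II), and the DSMB may un-blind whatever it needs (sections 9.1.3 and 10.1). No data are lost and no subject is monitored less closely.

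Most of this stands, and it limits the practical harm: the figure of 0 placebo subjects follows from a literal reading and is not an expected loss of data. It does not cure the definition. The wording appears twice, the protocol elsewhere distinguishes Tat from placebo, and no other safety set exists. An analysis set should be fixed by its own definition before unblinding, and not inferred from other sections afterwards.

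It is also fair to say that allocating subjects by product actually received is a separate question, on which the protocol is silent and which a statistical analysis plan commonly settles. Naming both products is enough to remove the contradiction.

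**Conclusion.** The concern holds. As defined in section 12.4 and the synopsis, the safety population contains about 100 Tat recipients and 0 placebo recipients out of 200, and the comparative safety objective cannot be met in it. The size assumes full planned enrolment, 1:1 allocation and dosing as randomized; it describes the population as worded, not the data collected. The definition contradicts sections 3, 8.2 and 12.7. It must be corrected because it governs the only secondary objective. An analysis plan that follows it inherits the error, and one that silently departs from it disagrees with the protocol on who is analysed for safety.

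**What to change.** In section 12.4 and in the synopsis, redefine the safety population as: *every randomized subject given one or more administrations of investigational product, whether Tat or placebo*. It is conventional to add that subjects are grouped by the product they actually received. That addition is sensible but is not needed to resolve the contradiction, and it could be placed in the statistical analysis plan instead.

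The change should be in place before database lock and unblinding, and any statistical analysis plan should carry the same wording. The cost is one sentence in two places. It needs no new data, adds no burden for subjects and leaves the sample size as it is.

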### 12.5 Methods

Continuous data will be summarized using descriptive statistics including N, mean, standard deviation, minimum, medium and maximum. Categorical data will be presented using N and %. 95% confidence intervals will be determined for all data.

All statistical analyses will be performed at a 5% significance level and will be 2-tailed.

### 12.6 Primary Endpoint Analysis

*To evaluate the **humoral immune response** to vaccination, “responders” will be defined as those vaccinated subjects that develop an immune response greater than the following levels:*

- *Anti-Tat IgM titers  $\geq 25$*
- *Anti-Tat IgG titers  $\geq 100$*
- *Anti-Tat IgA titers  $\geq 25$*

*The percentage of responders will be compared between active and placebo groups using the Chi-Square test. Additionally, geometric mean antibody titers (GMT) will be calculated and compared between treatment groups by using a t-Test for unpaired data.*

### 12.7 Secondary Endpoint Analysis

Changes from baseline in physical examination results, vital signs data and laboratory parameters will be summarized for both treatment groups.

MedDRA dictionary will be used for coding adverse events. Adverse events will be summarized by system organ class, preferred term, severity and relationship with the

vaccination; the incidence of adverse events “possibly”, “probably” or “certainly” related to vaccination will be computed. All serious adverse events (SAEs) will be summarized by treatment group, subject, gender, age, duration of the event, action taken, investigator’s assessment of causality and outcome.

Change from baseline will be summarized for CD4+ T cells and HIV viral load. Haematology, clinical chemistry and urinalysis results will be graded according to Appendix I and will be presented for both treatment groups.

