Assessment of safety was performed at baseline and at several time points during the study. Overall, no clinically significant alterations in laboratory values have been identified in any treatment group. AEs were coded according to the MedDRA dictionary and grouped in accordance to the MedDRA System Organ Classes (SOC). An independent, “ad hoc” safety monitoring board periodically evaluated all safety documentation including the frequency and characteristics of AEs. Safety monitoring confirmed that the vaccine based on the recombinant Tat protein is safe and well tolerated. The most frequent AEs were mild and did not appear to be clearly dose related, including injection site reactions, asthenia, fever, headache and transient blood disorders (mainly leukocytosis and neutrophilia).

Vaccination efficiently induced both humoral and cellular immune responses against the Tat protein (Ensoli et al AIDS 2008 and Vaccine 2009, Longo et al Vaccine 2009, Bellino et al Rev Rec Clin Trials 2009). In particular, in HIV-infected asymptomatic individuals, intradermal vaccination with Tat (given 5 times on a monthly schedule), in the absence of adjuvant, not only induced functional antibodies, but also partially reverted the marked Th1 polarization of anti-Tat immunity seen in natural infection eliciting a more balanced Th1/Th2 immune response (Ensoli et al AIDS 2008, Longo et al Vaccine 2009). Remarkably, the number of CD4+ T cells had a significant positive correlation with anti-Tat antibody titers, which persisted up to 144 weeks after the first vaccination (Ensoli et al Vaccine 2009, Longo et al Vaccine 2009, Bellino et al Rev Rec Clin Trials 2009).

Based on these data, a phase II therapeutic, open label, clinical study with Tat protein (ISS T-002, ClinicalTrials.gov NCT00751595) was sponsored by ISS and activated in 10 clinical sites in Italy in HIV-infected HAART-treated subjects negative for anti-Tat antibodies at baseline, with undetectable viral load and no evidence of virological rebounds (viral <50 copies/ml in the last 6 months before enrolment), with CD4+ T cell counts >400 cells/μl and a CD4 nadir >250 cells/μl. In this study, subjects are randomized into two arms to receive 3 or 5 vaccinations monthly; each arm is composed of two treatment groups, receiving 7, 5 or 30 μg of Tat, respectively.

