#### **Haematology:**

Red cell count, haemoglobin, haematocrit, MCV, platelets, white cell count and differential counts (neutrophils, lymphocytes, monocytes, eosinophils, basophils)

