| Visual changes (from baseline)                                              | Visual changes causing no or minimal interference with usual social & functional activities              | Visual changes causing greater than minimal interference with usual social & functional activities              | Visual changes causing inability to perform usual social & functional activities              | Disabling visual loss in affected eye(s)                                                         |
| HEMATOLOGY Standard International Units are listed in italics |                                                                                                          |                                                                                                                 |                                                                                               |                                                                                                  |
| Absolute neutrophil count (ANC)                                             | 1,000 – 1,300/mm 
1.000 x 10^9 – 1.300 x 10^9/L                | 750 – 999/mm 
0.750 x 10^9 – 0.999 x 10^9/L                           | 500 – 749/mm 
0.500 x 10^9 – 0.749 x 10^9/L         | < 500/mm 
< 0.500 x 10^9/L                                    |
| Fibrinogen, decreased                                                       | 100 – 200 mg/dL
1.00 – 2.00 g/L
OR
0.75 – 0.99 x LLN                                     | 75 – 99 mg/dL
0.75 – 0.99 g/L
OR
0.50 – 0.74 x LLN                                              | 50 – 74 mg/dL
0.50 – 0.74 g/L
OR
0.25 – 0.49 x LLN                            | < 50 mg/dL
< 0.50 g/L
OR
< 0.25 x LLN
OR
Associated with gross bleeding |
| Hemoglobin (Hgb)
( HIV POSITIVE ONLY )                            | 8.5 – 10.0 g/dL
5.24 – 6.23 mmol/L                                                             | 7.5 – 8.4 g/dL
4.62 – 5.23 mmol/L                                                                     | 6.50 – 7.4 g/dL
4.03 – 4.61 mmol/L                                                  | < 6.5 g/dL
< 4.03 mmol/L                                                            |

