| Partial Thromboplastin Time (PTT)                                            | 1.1 – 1.66 x ULN                                                                                         | 1.67 – 2.33 x ULN                                                                                    | 2.34 – 3.00 x ULN                                                                                    | > 3.00 x ULN                                                                |
| Platelets, decreased                                                         | 100,000 –
124,999/mm 
100.000 x 10^9 –
124,999 x 10^9/L | 50,000 –
99,999/mm 
50.000 x 10^9 –
99,999 x 10^9/L | 25,000 –
49,999/mm 
25.000 x 10^9 –
49,999 x 10^9/L | < 25,000/mm 
< 25.000 x 10^9/L           |
| WBC, decreased                                                               | 2,000 – 2,500/mm 
2.000 x 10^9 –
2.500 x 10^9/L            | 1,500 – 1,999/mm 
1.500 x 10^9 –
1.999 x 10^9/L        | 1,000 – 1,499/mm 
1.000 x 10^9 –
1.499 x 10^9/L        | < 1,000/mm 
< 1.000 x 10^9/L             |
| CHEMISTRIES Standard International Units are listed in italics |                                                                                                          |                                                                                                      |                                                                                                      |                                                                             |
| Albumin, serum, low                                                          | 3.0 g/dL – < LLN
30 g/L – < LLN                                                             | 2.0 – 2.9 g/dL
20 – 29 g/L                                                                 | < 2.0 g/dL
< 20 g/L                                                                     | NA                                                                          |

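### The graded haematology table scores only falls in white cells and neutrophils, so it cannot show the rises that the protocol reports from earlier trials of this vaccine

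*Protocol*

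**What the plan says.** Section 12.7 of the protocol plans two laboratory outputs by arm. One is a summary of changes from baseline in laboratory parameters. The other is a graded presentation: "Haematology, clinical chemistry and urinalysis results will be graded according to Appendix I and will be presented for both treatment groups".

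Appendix I has one row for total white cells, headed "WBC, decreased", and one for neutrophils, headed "Absolute neutrophil count (ANC)". Both assign Grades 1 to 4 to progressively lower counts. Neither has a counterpart for raised counts. Both quantities are measured: the haematology panel in section 6.6.2 includes "white cell count and differential counts (neutrophils, lymphocytes, monocytes, eosinophils, basophils)".

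Section 2.1 describes the safety findings of the earlier trials. Among the most frequent adverse events it names "injection site reactions, asthenia, fever, headache and transient blood disorders (mainly leukocytosis and neutrophilia)". It qualifies this in two ways: "The most frequent AEs were mild and did not appear to be clearly dose related", and "Overall, no clinically significant alterations in laboratory values have been identified in any treatment group".

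**The concern.** Safety against placebo is the trial's only secondary objective (section 3), and the graded laboratory table is one of the displays that will carry it. Its scale has no place for the direction of white-cell change that the protocol itself reports from earlier trials. If one arm had more subjects with raised counts than the other, the graded table would look the same as if there were no difference. A reader who took that table as the haematological safety comparison could conclude that nothing happened to white cells, when the scale could not have shown it.

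**Working it through.** The plan states no figure on this point, so there is nothing to reproduce. The check applies the printed scale and then follows a raised count through each planned output.

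**Step 1: the scale (Appendix I, per mm³).**

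| Row | Grade 1 | Grade 2 | Grade 3 | Grade 4 |
|---|---|---|---|---|
| White cells | 2,000–2,500 | 1,500–1,999 | 1,000–1,499 | below 1,000 |
| Neutrophils | 1,000–1,300 | 750–999 | 500–749 | below 500 |

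**Step 2: apply it.** The test values are illustrations chosen for this check, not data from the documents.

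- White cells of 2,300, 1,700, 1,200 and 900 receive Grades 1, 2, 3 and 4. White cells of 6,000, 12,000, 20,000 and 50,000 receive no grade.
- Neutrophils of 1,200, 800, 600 and 400 receive Grades 1, 2, 3 and 4. Neutrophils of 4,000, 9,000, 15,000 and 40,000 receive no grade.

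A markedly raised count and a normal count are therefore indistinguishable in the graded output.

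**Step 3: is one-way grading general in Appendix I?** No. Calcium, glucose, potassium and sodium each have a high row and a low row.

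**Step 4: how many samples are affected?** Appendix II schedules haematology at screening, Day 0, and Days 7, 35, 63, 84, 112, 140, 168 and 336. That is 10 visits in all, and 10 − 2 = 8 after the first dose. The limitation applies to all 8.

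**Step 5: where would a raised count appear?**

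| Planned output | Can it show a rise? | Does it count affected subjects per arm? |
|---|---|---|
| Appendix I grades (12.7) | No | Not for rises |
| Adverse events (9.2.1, 9.3, 12.7) | Yes, if reported as an event | Yes, for reported events only |
| Change from baseline (12.7, summarised as in 12.5) | Yes | No |

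On the adverse-event route, section 9.2.1 gives two examples that bear on laboratory results: an increase in toxicity grade on the Appendix I table, and a clinically significant change in a safety parameter. A raised white-cell or neutrophil count can never meet the first, because it has no grade. In practice it rests on the investigator's judgement under the second.

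On the change-from-baseline route, section 12.5 specifies N, mean, standard deviation, minimum, a middle value printed as medium (presumably the median) and maximum, with 95% confidence intervals. A general upward shift would move the mean, and one large rise would set the maximum. None of these statistics gives the number of subjects per arm who moved above the normal range.

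**The case against.** The strongest reply is that the graded table is only one of several safety outputs.

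- **Change from baseline** is summarised by arm in both directions and is not tied to Appendix I. This stands. What it lacks is a count of subjects.
- **Adverse events.** The opening definition in section 9.2.1 is broad and takes in abnormal laboratory findings. Section 9.3.1 gives a severity rule for events outside the toxicity table, and section 12.7 tabulates events by preferred term and severity. The rises in section 2.1 were themselves reported as adverse events, so the route can work. This also stands in part. But sections 9.2.1 and 9.3 attach clinical significance to laboratory changes, and the reporting rule of the earlier trials is not given. Whether comparable rises would be reported here cannot be settled from the protocol.
- **Shift tables commonly belong in the statistical analysis plan**, which is not at hand. Fair, and nothing in section 12.7 forbids one. The point rests on what the protocol does fix: a named and printed scale that runs one way for these two counts.

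Some stronger readings are tempting, but the documents do not support them.

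- A reader might infer a known vaccine effect on white cells. Section 2.1 reports frequent, mild, transient events with no clear dose relation and no clinically significant laboratory alterations. It does not establish causation.
- A reader might say that a rise is scored as absence of toxicity, or that the table points the wrong way. Appendix I has Grades 1 to 4 only; a raised count is simply ungraded, and the table is silent on rises, not reversed.
- A reader might conclude that the safety comparison as a whole cannot show a difference. That is true only of the graded table with respect to rises.
- A reader might add that coagulation escapes grading because section 12.7 does not name it. The prothrombin and partial thromboplastin time rows stand under the haematology heading of Appendix I, so this is at most an ambiguity of label.

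**Conclusion.** The point holds in a limited form. The by-arm graded haematology table cannot register a rise in white cells or neutrophils at any of the 8 scheduled post-dose visits, although rises are the direction reported in section 2.1. A rise not judged clinically significant would be visible only in a continuous summary that does not count affected subjects.

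This rests on Appendix I being used as printed and on investigators applying the clinical-significance wording in sections 9.2.1 and 9.3. No difference between arms can be predicted, because the documents give no rate of leukocytosis or neutrophilia in either arm. The primary endpoint, its test and the sample size are unaffected. It is a worthwhile and cheap improvement to a secondary display, not a flaw that threatens the trial's conclusions.

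**What to change.** In section 12.7, add a shift table by treatment arm for white-cell count and neutrophils against the laboratory's upper limit of normal. Give the number and percentage of subjects who are not above the limit on Day 0 and are above it:

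- at any of the 8 scheduled post-dose haematology visits; and
- at each of Days 7, 35 and 63, the visits one week after each scheduled vaccination.

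The denominator is subjects with a Day 0 value not above the limit and at least one post-dose value (for the by-visit rows, a value at that visit). Appendix I can stay as it is; no new grade cut-offs are needed. If the statistical analysis plan already contains such a table, a cross-reference in section 12.7 is enough.

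The cost is a sentence or two in section 12.7 and one more table, from samples already scheduled. The safety display may look less favourable than the graded table alone.
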